### Sample size calculation

As reported in previous studies (8), the mean DHI score for patients treated with betahistine mesilate was 30. For the purpose of sample size estimation, we adopted the clinically meaningful difference derived from our primary comparison: manual acupuncture versus sham acupuncture, assuming a mean DHI score of 21 in the manual acupuncture group, 33 in the sham acupuncture group, with a standard deviation of 20. A 12-point difference in DHI total score between manual acupuncture and sham acupuncture was regarded as clinically meaningful, since the minimal clinically important difference (MCID) for DHI total score has been established as 11 points (26). The trial will include three groups in a 1:1:1 ratio. Using a twotailed test with a category 1 error of 0.05 and a statistical efficacy of 90%, One-Way Analysis of Variance (ANOVA) F-Tests was employed by PASS software (Power Analysis and Sample Size, version 15). The calculations indicate that a minimum of 66 participants per group is required, totaling 198 participants across all groups. Accounting for an estimated drop out rate of 15%, the total sample size should be increased to 234 participants, with at least 78 participants per group.

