### Statistical analysis

Analyses for this study will be conducted in accordance with both the intention-to-treat (ITT) principle and the per-protocol set (PPS) approach. The ITT analysis will include all randomized participants, and the missing data will be imputed using the Last Observation Carried Forward (LOCF) method, with the most recent observed data carried forward for filling. The PPS will include participants who have completed at least 80% of the prescribed treatment. SPSS 23.0 software will be used for statistical analysis. Quantitative indicators are described using mean, standard deviation, median, 25th percentile and 75th percentile. Categorical indicators are described using frequencies and percentages.

To control the Type I error caused by multiple comparisons, the Bonferroni correction will be adopted for pairwise comparisons of the primary outcome (DHI total score) among the three groups (manual acupuncture vs. sham acupuncture, manual acupuncture vs. western medication, sham acupuncture vs. western medication), with the adjusted significance level set at *p* < 0.017 (0.05/3); for secondary outcomes (DARS scores, dizziness diary indicators including attack frequency, duration and severity), the false discovery rate (FDR) method will be used for multiple comparison correction to balance the Type I and Type II error rates in exploratory analysis of multiple secondary indicators.

Since this study is a multicenter clinical trial, sub-center and corresponding baseline values were incorporated as covariates in the generalized linear model for analysis. Additionally, binary logistic regression was employed to analyze the impact of high versus low expectations on the primary efficacy endpoint across groups. The dependent variable in this analysis was response status, defined as participants showing at least a 50% reduction in total DHI scale score from baseline after 3 weeks of treatment (referred to as responders). The independent variable was the level of expectation (high or low).

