
Given that betahistine is commonly used in the clinical management of vertigo following PCIS, we have also included a medication control group treated with this drug, allowing for a comparative evaluation of the efficacy of acupuncture versus standard pharmacological therapy. While betahistine is predominantly indicated for peripheral vestibular disorders, its inclusion as an active comparator in this trial is methodologically sound and clinically informative for central vascular vertigo. This choice does not imply an assumption of superior efficacy but rather reflects real-world clinical practice, where no guideline-directed pharmacotherapy exists for PCIS with vertigo. Using the most widely adopted clinical agent as a comparator enables a pragmatic effectiveness comparison rather than an explanatory efficacy trial, which is more generalizable to routine care. Furthermore, our three-group design with true acupuncture, sham acupuncture, and betahistine permits simultaneous dissection of specific needling effects, non-specific placebo responses, and the actual clinical performance of standard care. Even if betahistine shows only mild or placebo-like effects in this study population, our trial will still produce high-quality evidence to clarify the added value of acupuncture and support evidence-based clinical decisions for these patients.

Notably, the present three-arm trial was established with a hierarchical study objective design to clearly differentiate explanatory from comparative effectiveness purposes. The primary comparison between manual acupuncture and sham acupuncture was specifically designated to evaluate the specific efficacy of acupuncture, whereas comparisons between acupuncture and western medication were defined as secondary analyses. This clearly predefined hierarchical structure minimizes potential ambiguity in the interpretation of study outcomes and reinforces the scientific validity and rigor of the trial design.

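### The 90% power belongs to a three-arm omnibus ANOVA at 0.05; the planned manual-versus-sham test at 0.05/3 has about 84.5%, and the equal alpha split does not fit the declared hierarchy

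*Protocol article*

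**What the plan says.** **Sizing (Sample size calculation).** The section says that it rests on the manual-versus-sham comparison, "assuming a mean DHI score of 21 in the manual acupuncture group, 33 in the sham acupuncture group, with a standard deviation of 20". It also gives a betahistine figure: "the mean DHI score for patients treated with betahistine mesilate was 30". The error rate is unadjusted, "Using a twotailed test with a category 1 error of 0.05", and the power and method are given as "a statistical efficacy of 90%, One-Way Analysis of Variance (ANOVA) F-Tests was employed by PASS software". The result is that "a minimum of 66 participants per group is required, totaling 198 participants across all groups", raised to 78 per group and 234 in total for 15% dropout.

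**Decision rule (Statistical analysis).** Here "the Bonferroni correction will be adopted for pairwise comparisons of the primary outcome (DHI total score) among the three groups". The three pairs are listed as manual versus sham, manual versus medication and sham versus medication, each judged at p < 0.017 (0.05/3). No omnibus test of the DHI is specified.

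**Hierarchy (Abstract, Introduction, Discussion).** The Abstract makes manual versus sham the primary comparison and places acupuncture versus medication second. The objectives at the end of the Introduction follow that order and do not include sham versus medication. The Discussion repeats it ("The primary comparison between manual acupuncture and sham acupuncture was specifically designated to evaluate the specific efficacy of acupuncture") and describes the structure as predefined and hierarchical.

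**The concern.** The test used for sizing, the test used for the decision and the declared ranking of comparisons should describe one design. Here they describe three:

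- an omnibus test at 0.05;
- three equally weighted pairwise tests at 0.05/3;
- a single primary contrast with the others ranked below it.

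Two things are at stake. First, the stated 90% may not be the power of the primary comparison. Second, the success criterion is ambiguous: a manual-versus-sham result of p = 0.03 would fail the Bonferroni rule, yet it would meet the 0.05 level at which the trial was sized.

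**Working it through.** **Inputs, all from the protocol article.** Means 21 (manual), 33 (sham) and 30 (betahistine); SD 20; alpha 0.05 two-sided for sizing; 66 evaluable per group; 15% dropout; 0.05/3 per pairwise test.

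**1. Reproduce the plan's figure.** For a one-way ANOVA with k = 3 groups, the noncentrality is λ = n·Σ(μᵢ − μ̄)²/SD², with 2 and 3(n − 1) degrees of freedom.

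- Mean of means: (21 + 33 + 30)/3 = 28.
- Sum of squares: (−7)² + 5² + 2² = 78.
- n = 65: λ = 65 × 78/400 = 12.675, power 89.6%.
- n = 66: λ = 66 × 78/400 = 12.87, power 90.05%.

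So 66 is the smallest n that reaches 90%, as stated. Dropout: 66/0.85 = 77.6, giving 78 per group and 234 in total, also as stated. A two-group t-test for 12 points gives a different n: 60 per group at 0.05 (59 gives 89.8%), or 77 at 0.05/3.

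**2. Dependence on the third arm.** With 66 per group, omnibus power changes with the medication mean, while the manual-versus-sham contrast does not:

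| Medication mean | Omnibus power at 0.05 |
|---|---|
| 30 (plan) | 90.05% |
| 27 (midpoint of 21 and 33, least favourable) | 87.5% |
| 21 or 33 | 95.2% |

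**3. Power of the planned pairwise tests.** Two-sided two-sample t-test with noncentrality δ/(SD·√(2/n)) and 2(n − 1) = 130 degrees of freedom. For 12 points: 12/(20 × √(2/66)) = 3.447. The critical value is 1.978 at 0.05 and 2.425 at 0.05/3.

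| Comparison | Difference | Power at 0.05 | Power at 0.05/3 |
|---|---|---|---|
| Manual vs sham | 33 − 21 = 12 | 92.8% | 84.5% |
| Manual vs medication | 30 − 21 = 9 | 72.8% | 56.5% |
| Sham vs medication | 33 − 30 = 3 | not needed | 6.2% |

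At exactly 0.017 the primary figure is 84.7%. With the error variance pooled over three groups it is 84.8%.

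**4. Sample size for 90% at 0.05/3.** 77 evaluable per group are needed; 77/0.85 = 90.6, so 91 randomized per group and 273 in total.

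**5. Sensitivity, manual versus sham at 0.05/3.** The documents give no baseline correlation r, so r is assumed, with SD replaced by 20·√(1 − r²).

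| Scenario | Power |
|---|---|
| 66 per group, r = 0.3 | 88.1% |
| 66 per group, r = 0.4 | 90.7% |
| 66 per group, r = 0.5 | 93.8% |
| All 78 analysed, full 12-point difference kept | 90.6% |
| All 78 analysed, 15% carry no difference (0.85 × 12 = 10.2), SD 20 | about 78% |

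**The case against.** The strongest reply is that 84.5% is only one scenario. The plan analyses all randomized participants with last observation carried forward, and at 78 per group power is 90.6%. It also adjusts for baseline, which restores about 90% if the baseline correlation is near 0.4. Further, Bonferroni is valid, a ranking of objectives need not imply a gatekept test sequence, and the Discussion gives the three-arm comparison a purpose that could cover sham versus medication. Finally, the protocol claims no power for the two medication comparisons.

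Much of this is fair as far as it goes. There is no inflation of type I error, and the low power for the medication comparisons contradicts no stated figure. Adjustment may well recover power. But the 90.6% spends the dropout allowance that the plan itself sets aside, and it assumes that carried-forward values keep the full effect; if the 15% carry none, power is about 78%. The sample size section takes no credit for baseline adjustment and gives no correlation. None of these routes is the calculation that the plan reports. Ranked objectives can coexist with Bonferroni, but an equal split that includes a pair outside the listed objectives does not carry out the hierarchy that the Discussion says removes ambiguity.

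**Conclusion.** The concern holds. The arithmetic behind 66, 198, 78 and 234 is correct, but it answers a question that the analysis does not ask. For the declared primary comparison under the declared decision rule, power is 84.5%, a shortfall of 5.5 percentage points (type II error about 15.5% instead of 10%). This rests on the plan's 12-point difference, SD 20 and 66 evaluable per group, in an unadjusted comparison. With baseline adjustment it would be 88% to 94% for assumed correlations of 0.3 to 0.5. The conflict between the equal alpha split and the ranked comparisons stands whatever the correlation. It should be settled before unblinding, because it determines what counts as a positive trial.

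**What to change.** Preferred change, in the Sample size calculation and Statistical analysis sections:

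- Make manual versus sham on total DHI the only primary confirmatory test, at two-sided 0.05, and name the single visit at which it is made.
- Test manual versus medication at two-sided 0.05 only if the first test succeeds (fixed sequence, which keeps the familywise error at 0.05).
- Report sham versus medication as an estimate with a confidence interval, and delete the 0.017 rule.
- Restate the sample size as a two-group comparison: 66 evaluable per group give about 93% power for 12 points, and about 73% for manual versus medication at 9 points.

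This costs wording and no extra participants. The downside is that no confirmatory claim against medication can be made if the primary test fails.

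If Bonferroni is kept, state the power of manual versus sham as about 84.5% with its assumptions, or plan 77 evaluable (91 randomized) per group. The latter adds 273 − 234 = 39 participants.

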### Data management and confidentiality

The case report form (CRF) for each participant will be promptly completed and subsequently reviewed and entered into a secure database by an individual not involved in the treatment. To ensure confidentiality, all personal information, including names, phone numbers, and addresses, will be anonymized to prevent any disclosure. The CRF will include key data points such as observation time points, imaging time points, outcome measures, adverse events, and safety assessments. Researchers are required to complete the CRFs accurately and in a timely manner according to the specified protocol. All participant data will be securely stored in a locked cabinet by the research team and retained for at least 5 years after publication in a medical journal. This ensures compliance with data protection regulations and allows for future reference and verification.

### Statistical analysis

Analyses for this study will be conducted in accordance with both the intention-to-treat (ITT) principle and the per-protocol set (PPS) approach. The ITT analysis will include all randomized participants, and the missing data will be imputed using the Last Observation Carried Forward (LOCF) method, with the most recent observed data carried forward for filling. The PPS will include participants who have completed at least 80% of the prescribed treatment. SPSS 23.0 software will be used for statistical analysis. Quantitative indicators are described using mean, standard deviation, median, 25th percentile and 75th percentile. Categorical indicators are described using frequencies and percentages.

To control the Type I error caused by multiple comparisons, the Bonferroni correction will be adopted for pairwise comparisons of the primary outcome (DHI total score) among the three groups (manual acupuncture vs. sham acupuncture, manual acupuncture vs. western medication, sham acupuncture vs. western medication), with the adjusted significance level set at *p* < 0.017 (0.05/3); for secondary outcomes (DARS scores, dizziness diary indicators including attack frequency, duration and severity), the false discovery rate (FDR) method will be used for multiple comparison correction to balance the Type I and Type II error rates in exploratory analysis of multiple secondary indicators.

Since this study is a multicenter clinical trial, sub-center and corresponding baseline values were incorporated as covariates in the generalized linear model for analysis. Additionally, binary logistic regression was employed to analyze the impact of high versus low expectations on the primary efficacy endpoint across groups. The dependent variable in this analysis was response status, defined as participants showing at least a 50% reduction in total DHI scale score from baseline after 3 weeks of treatment (referred to as responders). The independent variable was the level of expectation (high or low).

Neuroimaging data (sMRI and ASL-MRI) will be analyzed with professional software and standardized methods, and all analyses will be completed by an experienced radiologist who is blinded to the participant group allocation. sMRI data will be preprocessed and analyzed using SPM12 (Statistical Parametric Mapping 12) and FSL (FMRIB Software Library); the preprocessing steps include skull stripping, spatial normalization, tissue segmentation (gray matter, white matter, cerebrospinal fluid) and 8 mm Gaussian kernel smoothing, and then voxel-based morphometry (VBM) and voxel-mirrored homotopic connectivity (VMHC) will be used to analyze group differences in gray matter volume (GMV), cortical thickness and interhemispheric functional connectivity. ASL-MRI data will undergo motion correction, distortion correction and arterial transit time (ATT) correction to calculate cerebral blood flow (CBF) maps; region of interest (ROI) analysis will be performed on vestibular-related brain regions (vestibular nuclei, brainstem, cerebellum, posterior cerebral cortex) to compare group differences in regional CBF, and whole-brain voxel-wise analysis will be conducted to explore potential brain regions with altered perfusion associated with vertigo improvement.

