**Methods and design:**

This is a multicenter, randomized, controlled trial that will randomly allocate 234 participants in a 1:1:1 ratio to manual acupuncture group, sham acupuncture group, or western medication group. This trial is primarily designed as an explanatory trial, with the primary comparison being manual acupuncture vs. sham acupuncture to evaluate the specific efficacy of acupuncture; comparisons between acupuncture and western medication are regarded as secondary comparative effectiveness analyses. All groups will receive standard secondary stroke prevention. Manual and sham acupuncture will be administered five times weekly for 3 weeks (30 min/session), while the western medication group will receive oral betahistine mesilate tablets three times daily, 5 days per week, for 3 weeks. Assessments will be conducted at baseline (Week 0), post-treatment (Week 3), and at Week 11. The primary outcome is the Dizziness Handicap Inventory (DHI); secondary outcomes include the Dizziness and Anxiety Rating Scale (DARS), dizziness diaries and adverse event rate during the follow-up period. To test the *a priori* hypothesis that acupuncture improves dizziness by modulating posterior circulation hemodynamics and regional cerebral perfusion in vestibular-related brain regions, cerebral hemodynamics and brain imaging changes will be assessed using transcranial Doppler (TCD), structural magnetic resonance imaging (sMRI), and arterial spin labeling MRI (ASL-MRI) at baseline (Week 0) and post-treatment (Week 3). We specifically hypothesize that acupuncture will increase mean flow velocity (MFV) and reduce resistance index (RI) in the vertebral arteries, basilar artery, and posterior cerebral arteries, enhance regional cerebral perfusion in vestibular-related brain areas, and induce structural changes associated with vestibular compensation.

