Currently, for patients with PCIS accompanied by vertigo, clinicians typically use medications such as betahistine. Given the absence of disease-specific, evidence-based pharmacotherapy for vertigo associated with PCIS, we selected betahistine as the comparator in this trial. Although betahistine is most widely studied in peripheral vestibular disorders such as Ménière’s disease, it remains the most commonly prescribed agent for central vascular vertigo in clinical practice, particularly for patients with vertebrobasilar insufficiency. Betahistine acts as a partial agonist at H2 receptors and an agonist at H1 receptors, exerting significant vasodilatory effects on cerebral, coronary, and peripheral vessels, particularly the vertebrobasilar system, thereby increasing blood flow to the brain, heart, and peripheral tissues (6). Meanwhile, it acts as an H3 receptor antagonist to improve central vestibular compensation (7, 8). These dual mechanisms provide a biologically plausible rationale for its use in PCIS with vertigo. As no definitive first-line medication exists for this indication, betahistine represents the most pragmatic and clinically relevant choice to enable a direct comparison with acupuncture. However, achieving long-term control and improvement of vertigo symptoms with betahistine typically requires both high doses and prolonged administration (9). Clinical studies indicate that existing pharmacological treatments provide limited efficacy evidence for managing vertigo associated with PCIS, and symptoms frequently recur upon discontinuation of the medication (10). Additionally, polypharmacy in stroke patients may reduce adherence, increase drug resistance, and impose extra physical and psychological burdens, highlighting the critical need for safe, effective, and well-tolerated non-pharmacological interventions.

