## Patients and methods

### Study design

This randomized, three-armed, parallel-controlled, multicenter clinical trial was approved by the Medical Ethics Committee of the Affiliated Hospital of Chengdu University of Traditional Chinese Medicine (approval number: 2024KL-021) and registered with the China Clinical Trial Registration Center (registration number: ChiCTR2400087030; https://www.chictr.org.cn/), prior to the enrollment of the first participant. The protocol adheres to the SPIRIT statement. The future trail will carry out in accordance to the Declaration of Helsinki and follow the Consolidated Standards of Reporting Trials (CONSORT) guidelines (19), including the STRICTA extension for reporting interventions in clinical trials of acupuncture (20).

All participants are coming from 3 tertiary hospitals in Sichuan Province, China: the Affiliated Hospital of Chengdu University of Traditional Chinese Medicine, Chengdu Shuangliu District Hospital of Traditional Chinese Medicine and Chengdu Longquanyi District Hospital of Traditional Chinese Medicine. The study period comprised a 1-week baseline phase, a 3-weeks treatment phase, and an 8-weeks follow-up phase. A flow chart outlining the trial design is presented in Figure 1, while details on patient enrollment, intervention, and assessment times are shown in Table 1.

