#### Primary outcome

The Dizziness Handicap Inventory (DHI) is the most widely used self-reported measure for assessing dizziness across three domains (25): physical (DHI-P, maximum score of 28), emotional (DHI-E, maximum score of 36), and functional (DHI-F, maximum score of 36). Each item is scored as 0 (no), 2 (sometimes), or 4 (yes). The total score, ranging from 0 to 100, is calculated by summing the scores of all items, with higher scores indicating more severe the dizziness disorder. These outcome measures will be repeatedly assessed at weeks 0, 3, and 11 by a researcher who is blinded to participant allocation.

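### LOCF fills every missing Week 3 DHI with the pre-treatment score, which shrinks a true acupuncture effect and biases the primary comparison if dropout differs by arm

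*Protocol article*

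**What the plan says.** Under Statistical analysis, the protocol article sets the population with "The ITT analysis will include all randomized participants" and the handling of missing values with "the missing data will be imputed using the Last Observation Carried Forward (LOCF) method, with the most recent observed data carried forward for filling". It names no other imputation. The DHI schedule is fixed under Primary outcome: "These outcome measures will be repeatedly assessed at weeks 0, 3, and 11". Table 1 agrees. Study design describes "a 3-weeks treatment phase, and an 8-weeks follow-up phase", so Week 3 is the end of treatment and Week 11 the end of follow-up.

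The abstract describes "the primary comparison being manual acupuncture vs. sham acupuncture to evaluate the specific efficacy of acupuncture". Sample size calculation plans on "assuming a mean DHI score of 21 in the manual acupuncture group, 33 in the sham acupuncture group, with a standard deviation of 20", cites an MCID of 11 points, and allows 15% dropout without splitting it by arm or by visit. Statistical analysis adjusts for centre and baseline and tests the three pairwise DHI comparisons at 0.05/3.

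**The concern.** With three measurement times, LOCF has very little to carry. A missing Week 3 score can only become the baseline score, which assumes that a patient lost during treatment did not change at all. A missing Week 11 score becomes the Week 3 score, or baseline if Week 3 is also missing.

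The planning means are 21 and 33. If baseline DHI lies above both, each filled value pulls its arm's mean up towards baseline. Equal losses pull both arms together and dilute a real effect. Unequal losses pull one arm further than the other and can move the difference in either direction, even when dropout is purely random within each arm. The filled values also enter the Week 3 responder analysis, where a carried baseline shows no reduction and so counts as a non-responder by construction.

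This concerns the estimate on which the trial's main claim rests. LOCF is stated outright as the rule, so it is not a detail left open for a later analysis plan.

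**Working it through.** **The plan's own figure.** One-way ANOVA with means 21, 33 and 30 (the last because "the mean DHI score for patients treated with betahistine mesilate was 30"), SD 20 and alpha 0.05. The grand mean is 28 and the squared deviations sum to 49 + 25 + 4 = 78, so the noncentrality at n = 66 per group is 66 × 78/400 = 12.87. Power is 0.9005 at 66 and 0.896 at 65, so 66 per group is right. 66/0.85 = 77.6, giving 78 per group and 234 in total. The stated sample size reproduces.

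**Inputs.** From the protocol: means 21 and 33, SD 20, MCID 11, dropout 15%, 78 per arm, test level 0.05/3 = 0.0167. My assumptions: the planning means apply at Week 3, mean baseline DHI is 50 (range shown), the correlation between baseline and Week 3 is 0.5, dropout is random within arm, and the split by arm and timing is as shown.

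**Expected Week 3 difference under LOCF.** With baseline mean B and the proportions missing Week 3 written dM (manual) and dS (sham):

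sham − manual = [(1 − dS) × 33 + dS × B] − [(1 − dM) × 21 + dM × B]

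With equal dropout d, B cancels and the difference is (1 − d) × 12:
- all 15% lost before Week 3: 0.85 × 12 = 10.2
- half of it (7.5%): 0.925 × 12 = 11.1
- the difference falls below 11 once d exceeds 1 − 11/12 = 8.3%

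With unequal dropout and a true difference of 12:
- 10% manual, 20% sham: 11.5 at B = 40, 12.5 at 50, 13.5 at 60
- 20% manual, 10% sham: 8.9, 7.9 and 6.9

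**Power at 0.0167.** Simulated baseline-adjusted ANCOVA, 78 randomised per arm, B = 50. Observed-data ANCOVA stands in for a likelihood-based analysis under ignorable missingness.

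| Missing Week 3, each arm | LOCF estimate | LOCF power | Observed-data estimate | Observed-data power |
|---|---|---|---|---|
| 15% | 10.2 | about 85% | 12.0 | about 93% |
| 7.5% | 11.1 | about 92% | 12.0 | about 96% |

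**No true effect.** With both arms at 33, the spurious difference is (dS − dM) × (B − 33). For 10% manual and 20% sham, with type I error simulated at nominal 1.67%:
- B = 45: 0.10 × 12 = 1.2 points, about 3%
- B = 50: 0.10 × 17 = 1.7 points, about 4%
- B = 60: 0.10 × 27 = 2.7 points, about 6%

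Reversing the split gives 1.7 points against acupuncture at B = 50, with the same inflation. Observed-data ANCOVA at 10%/20% gives no bias and about 1.6%. LOCF with 15% lost in each arm also gives about 1.6%, so there is no inflation.

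**Week 11.** Suppose all missingness falls between Weeks 3 and 11, and the arms relapse by rM and rS points after treatment. The bias in the sham − manual difference is dM × rM − dS × rS. It is zero if dropout and relapse are equal in both arms. For relapse of 0 to 10 points and splits of 15%/15%, 10%/20% and 20%/10%, it runs from −2.0 (0.10 × 0 − 0.20 × 10) to +2.0 (0.20 × 10 − 0.10 × 0). A patient lost before Week 3 has baseline carried to Week 11 as well, so the Week 3 mechanism persists there.

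**The case against.** The strongest reply is that the harm depends on dropout the protocol does not describe. The 15% is one trial-wide rate and eight of the eleven weeks come after treatment, so 10.2 is the extreme case. If half the losses come later, the difference stays just above the MCID. With equal dropout LOCF is conservative at Week 3 and keeps its type I error. Manual and sham participants are both blinded, and sham participants are offered acupuncture after the trial, so nothing in the document points to a 10%/20% split. A per-protocol analysis gives a partial cross-check. All of this stands and limits the size of the point. It does not rescue the rule: diluting a true effect is still bias, and protection against unequal dropout should not rest on hoping for equal dropout.

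A reader might infer three stronger things, which the document does not support.
- *That LOCF contradicts the protocol's own view of relapse.* The Introduction does say "symptoms frequently recur upon discontinuation of the medication", but in a sentence about drug treatment. It is in tension with carrying Week 3 to Week 11 for the betahistine arm and the two DHI comparisons that involve it. Nothing is said about relapse after manual or sham acupuncture, so there is no contradiction for the primary comparison.
- *That the bias reverses direction between Week 3 and Week 11.* At Week 11 it depends on relapse and dropout by arm, neither of which is given, and it can be zero.
- *That treating filled values as observed inflates type I error by itself.* Under equal dropout the simulation shows no inflation.

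The 66-to-78 inflation is routine and is not a separate error.

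**Conclusion.** The point holds for Week 3. With a true effect and equal dropout, LOCF attenuates the manual versus sham estimate by exactly the proportion missing at Week 3, whatever the common baseline: 12 becomes 10.2 at 15% and 11.1 at 7.5%. The cost in power is about 8 and 4 percentage points respectively, given baseline 50, SD 20 and correlation 0.5. With unequal dropout, the direction depends on which arm loses more patients. A 10-point gap in dropout produces a spurious 1.2 to 2.7 points for baselines 45 to 60 and roughly two to four times the nominal 1.67% error rate. The gap, the baseline and the correlation are assumptions, because the protocol gives none of them.

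For Week 11 the supported statement is only that LOCF can bias the estimate if relapse or dropout differs by arm. The rule should be changed, but it does not make the trial uninterpretable.

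**What to change.** Make the primary intention-to-treat analysis of DHI a likelihood-based mixed model for repeated measures at Weeks 3 and 11, with arm by visit, centre and baseline DHI, or use multiple imputation carried out by arm. If baseline enters only as a covariate, a participant with no DHI after baseline adds nothing to the mixed model. Multiple imputation, or a model that treats baseline as one of the responses, keeps all randomised participants in the analysis as the protocol intends.

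Both approaches assume that data are missing at random. Add a delta-adjusted or reference-based sensitivity analysis to probe that assumption, and keep LOCF at most as a further sensitivity analysis. State the choice before unblinding.

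The cost is a change of wording and modest programming. No new data, visits or participants are needed. The remaining weakness is the missing-at-random assumption itself, which the sensitivity analysis examines but cannot remove.
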